### Sample size and power

In the absence of evidence in published literature on which to derive sample size calculations in the context of an exploratory feasibility study, formal statistical power calculations have not been performed. An aim of exploratory studies is to determine feasibility of specific study aspects, subsequently allowing for estimation of sample sizes in the future studies.

The proposed sample size of 40 patients is a convenience-based sampling reflecting the annual estimate of patients with locally advanced cervical cancer likely to be eligible for this study at Mount Vernon Cancer Centre. From January 2019 to December 2019, there were a total of 30 patients with locally advanced cervical cancer treated with radical CRT. Assuming a conservative patient decline/withdrawal rate of 30%, the estimated annual number of complete study accruals is 21. This should enable a total number of 40 patients to be recruited over a period of 24 months. In a mixed population of cervix patients, a 2-year recurrence rate (local, nodal and distant) of 35% is assumed resulting in an estimated number of 14 events by the end of the study period.

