### Statistical analysis

Using logistic and Cox regression models the study will evaluate:

Different thresholds and temporal changes of fMRI parameters (DCE-MRI, DWI-MRI and BOLD-MRI) at various time points during cervical CRT can predict progression-free (local, nodal, distant) survival.Different thresholds and temporal changes of fMRI parameters (DCE-MRI, DWI-MRI and BOLD-MRI) at various time points during cervical CRT can predict response to treatment as defined by TVRR.Different thresholds and temporal changes of fMRI parameters (DCE-MRI, DWI-MRI and BOLD-MRI) at various time points during cervical CRT can predict overall survival.Different radiomics features can predict response to cervical CRT in terms of TVRR, progression-free (local, nodal, distant) survival and overall survival.Different thresholds and temporal changes of fMRI parameters (DCE-MRI, DWI-MRI and BOLD-MRI) at various time points during cervical CRT can predict changes in immunohistochemical markers of hypoxia and epithelial mesenchymal transition.

For each of the above regression analyses, a univariate logistic regression reporting the OR with 95% CI and p value from the likelihood ratio test will be performed. All covariates (fMRI parameters and radiomic features in table 1) and demographics) with a p<0.1 will be entered into a multivariate, forward conditional logistic regression and subsequently a p<0.05 will be considered statistically significant. The utility of the final prognostic model will be evaluated using sensitivity, specificity and area under the receiver operating characteristic curve.

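### Ordinary logistic regression on about 14 events can give infinite odds ratios for some of the strongest cut-offs, and it inflates the multivariable odds ratios

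*Protocol article*

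**What the plan says.** The Sample size and power section of the protocol article fixes the amount of information. "The proposed sample size of 40 patients is a convenience-based sampling", "a 2-year recurrence rate (local, nodal and distant) of 35% is assumed", and this is given as "resulting in an estimated number of 14 events by the end of the study period". It also says that "formal statistical power calculations have not been performed".

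The Statistical analysis section names logistic and Cox models and sets out to evaluate "Different thresholds and temporal changes of fMRI parameters (DCE-MRI, DWI-MRI and BOLD-MRI) at various time points" as predictors of progression-free survival, tumour volume reduction, overall survival and tissue markers. For each of these, "a univariate logistic regression reporting the OR with 95% CI and p value from the likelihood ratio test will be performed". Covariates with p<0.1 enter a forward conditional multivariable logistic model tested at p<0.05. The final model is judged by sensitivity, specificity and AUC.

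A likelihood ratio test with forward conditional selection and no penalty is ordinary maximum likelihood (ML). The article implies this but does not say so. It names no interval type (Wald or profile likelihood) and gives no rule for a cut-off that leaves an empty cell.

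**The concern.** Two properties of ML logistic regression matter with 14 events against 26 non-events.

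- **Empty cells.** If every patient who progresses falls on one side of a cut-off, or every patient who does not, the ML odds ratio is infinite. Cut-offs with very high sensitivity or specificity are the ones most exposed, and the primary outcome is framed in those terms. The likelihood ratio p value stays small, so the marker passes the p<0.1 screen and enters the multivariable model with a coefficient that has no finite estimate.
- **Small-sample bias.** ML log odds ratios lie on average too far from zero, and more so with each added covariate. The Future work section intends a risk model to be taken into a validation pilot and then a randomised dose-escalation study. Inflated coefficients would make that model look stronger than it is.

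Both belong to the estimator. They exist for a single pre-specified marker, although the empty-cell problem is then small unless the marker is very accurate.

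**Working it through.** **Inputs from the article.** 40 patients; 35% two-year recurrence; 30 eligible patients a year; 30% decline or withdrawal. The article gives no marker accuracy or effect size, so those below are assumptions, shown as ranges.

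**1. The plan's own figures.** Events: 40 × 0.35 = 14, leaving 26 non-events. Accrual: 30 × 0.70 = 21 a year, or 42 in 24 months. Both agree with the article.

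**2. Chance of an empty cell, cut-off fixed in advance.** With sensitivity *se* and specificity *sp*:

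P = 1 − (1 − se^14 − (1−se)^14) × (1 − sp^26 − (1−sp)^26)

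At 0.9/0.8: 0.9^14 = 0.229 and 0.8^26 = 0.003, the other terms being negligible, so P = 1 − 0.771 × 0.997 = 0.231.

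| se/sp | P(empty cell) |
|---|---|
| 0.7/0.7 | 0.7% |
| 0.8/0.8 | 4.7% |
| 0.9/0.8 | 23% |
| 0.9/0.9 | 28% |
| 0.95/0.9 | 52% |

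For rare-positive cut-offs (20–30% of events and 5% of non-events above) it is 27–30%.

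**3. Chance of an empty cell, cut-off searched.** Simulation of a binormal marker with AUC 0.6–0.9, 20,000 runs:

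- The cut-off with the largest likelihood ratio has an empty cell in 40–50% of runs; 26–50% with at least 4 patients per side, 3–41% with at least 10.
- The best-Youden cut-off has one in 9–25%.
- A median split has one in under 2% up to AUC 0.80, 6% at 0.85 and 18% at 0.90.
- A single continuous marker separates the groups in 0.1% of runs or fewer.

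**4. What is reported when a cell is empty.** The Firth estimate for a 2×2 table adds 0.5 to each cell.

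| Above cut-off | ML OR | LRT p | Profile 95% CI | Firth OR |
|---|---|---|---|---|
| 14/14 events, 10/26 non-events | infinite | 0.000012 | 9.5 to infinity | (14.5 × 16.5)/(0.5 × 10.5) = 45.6 |
| 5/14 events, 0/26 non-events | infinite | 0.0006 | 5.5 to infinity | (5.5 × 26.5)/(9.5 × 0.5) = 30.7 |

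**5. Bias when the estimate is finite.** For pre-fixed cut-offs with se/sp from 0.6 to 0.8, exact enumeration gives a mean ML log OR 5–7% too large (a true OR of 5.44 becomes 6.08). At extreme cut-offs the finite estimates are too small: 0.97 times the true log OR at 0.9/0.9, 0.89 at 0.95/0.9, and 0.83–0.87 for the rare-positive cut-offs. The mean Firth log OR is 1.00 times the truth for se/sp from 0.6 to 0.85; in the extreme settings it is 0.94–0.98.

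For continuous markers with true OR per SD from 1.65 to 4.48 (1,500 runs each), the mean log OR divided by the truth is:

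| Covariates | ML | Firth |
|---|---|---|
| 1 | 1.12–1.18 | 1.00–1.05 |
| 4 | 1.26–1.41 | 1.00–1.05 |
| 6 | 1.40–1.59 | 1.04–1.06 |

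The distributions are skewed, so medians are smaller. With four covariates and a true OR of 2.72 (log OR 1.0), the median ML OR is 3.10 and ln 3.10 = 1.13: a median inflation of 13% against a mean of 26%. Repeated simulations at OR 2.5 per SD gave mean inflation of 9–11% with one covariate and 38–40% with four, while Firth stayed at 0.97–1.03 times the truth.

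**The case against.** - **The interval type is not stated, and an article may leave it to a fuller document.** This stands in part. A reader might infer that the OR, interval and p value will contradict each other. That follows only with Wald intervals. The profile-likelihood interval, which matches the planned test, has lower limits of 9.5 and 5.5 in the examples and so agrees with the small p values. Only its upper limit is missing. But the article does fix the model, the reported quantity, the test and the selection method, and the infinite estimate follows from those.
- **Empty cells are uncommon at ordinary accuracy.** Correct: 0.7–5% at 0.7–0.8. A reader might infer that the best cut-offs always fail. They do not: it is a minority to about half of them, depending on accuracy, search criterion and minimum group size. The highest rates at moderate accuracy come from searching cut-offs, which is a separate weakness.
- **Univariate inflation is modest and can reverse.** Correct. It would be wrong to say that all remaining ORs are exaggerated. The multivariable step is where the bias is material, and even there a few nearly separated samples drive the mean. In one simulation with four covariates, 5% of runs exceeded three times the true value, and without them mean inflation fell from 38% to 20%.
- **The primary outcome can still be reported.** Correct. A cut-off with an empty cell has a sensitivity or specificity of 100%, and a single marker's AUC does not depend on the size of its OR.
- **The study is openly exploratory and unpowered.** True, but that is no reason to keep a biased estimator when a better one is readily available.

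**Conclusion.** The point holds in a limited form. Followed as written, the plan will give infinite ORs for some of the strongest-looking cut-offs: about 5% at 0.8/0.8, 23–52% from 0.9/0.8 to 0.95/0.9, and up to about half under a search for the largest likelihood ratio. Mean log ORs will be inflated by about 5–18% in univariate models and 26–41% with four covariates.

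These sizes rest on 14 events and 26 non-events and on assumed accuracies and effects. The number of covariates the selection will retain is unknown. The article gives no event count for overall survival or tumour volume reduction, so the problem cannot be sized for them, and no Cox calculation was made.

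A reader might infer that the study cannot report what it is looking for. The document does not support that: sensitivity, specificity and single-marker AUC are untouched. What suffers is the reported ORs and the multivariable model built on them. The change is worth making before analysis but does not undermine the study.

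**What to change.** State that all logistic models use Firth's penalised likelihood, with penalised profile-likelihood 95% CIs and penalised likelihood-ratio p values. The OR then exists and agrees with its interval and p value when a cell is empty. Apply the intercept-corrected version (FLIC) only where predicted probabilities are compared with a probability cut-off to obtain sensitivity and specificity; it changes the intercept alone and so leaves AUC as it was. In Cox models, use Firth's method where a group has no events.

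The cost is one sentence and standard routines in R or SAS. Estimates move slightly towards 1, and the forward selection has to be coded because a menu procedure may not offer the penalised test. Optimism from choosing the best cut-off and from the p<0.1 screen remains and needs its own remedy.

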This has been clarified in a systematic review, which details prospective studies using different fMRI techniques in cervical cancer. DWI and DCE-MRI represent the most used techniques, followed by BOLD-MRI. Furthermore, the majority of studies evaluated a single technique rather than a combination. This has led to a lack of consensus confounded by ‘multiple interacting factors, including histology, grade, hypoxia, vascularity and cellularity that can influence fMRI-derived parameters’. To account for this, future studies will need to employ combinations of fMRI techniques to generate ‘a more holistic assessment of the tumour, simultaneously assessing multiple tumour features to improve outcome prediction. Refinement of fMRI as a predictive and prognostic marker can be improved further by combining clinicopathological scoring and or genomic signatures for hypoxia.^6^

In addition to a multiparametric approach, fMRI needs to be repeated across treatment to discern tumour response and relate it to fMRI-derived parameters. Spatial data can also be acquired—an example of which DCE-MRI can identify a ‘functional risk volume’ within the tumour associated with poorer response to treatment. Tumours with a ‘functional risk volume’ displayed poor vascularity and tumour permeability.^7^ More recently, a study demonstrated combining DWI-derived and DCE-derived parameters to describe the ‘hypoxic fraction’ of cervical tumours linking this to disease-free survival.^8^

The Exploratory study of using Magnetic resonance Prognostic Imaging markers for Radiotherapy In Cervix cancer (EMPIRIC) study aims to build on previous studies and address the gaps in the current evidence base by performing multiparametric fMRI (DWI, DCE and BOLD-MRI) across treatment in patients with cervical cancer, alongside collection of blood samples for circulating tumour cell (CTC) and circulating tumour DNA (CtDNA) and tissue biopsies to facilitate parallel molecular analysis. This holistic approach to tumour characterisation will provide the tools to generate a meaningful predictive and prognostic model for personalised radiotherapy for cervical cancer.

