### Outcomes

#### Primary outcome

To evaluate sensitivity and specificity of quantitative parameters derived from DCE-MRI, DWI-MRI and BOLD-MRI as predictors of progression-free (local, nodal, systemic) survival at 2 years post-treatment in patients with locally advanced cervical cancer after CRT.

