#### Secondary outcomes

To evaluate sensitivity and specificity quantitative parameters derived from DCE-MRI, DWI-MRI and BOLD-MRI as predictors of overall survival at 2 years in patients with locally advanced cervical cancer after CRT.To evaluate sensitivity and specificity quantitative parameters derived from DCE-MRI, DWI-MRI and BOLD-MRI as predictors of the TVRR in response to CRT of patients with locally advanced cervical cancer.To apply radiomics for derivation of textural imaging features as predictors of progression-free (local, nodal, systemic), overall survival and TVRR after CRT for cervix cancer.To correlate temporal changes in quantitative MRI parameters during CRT with molecular markers from tissue biopsies and CTCs isolated from peripheral blood samples.To explore the feasibility of using quantitative MRI parameters to provide a roadmap in identifying high-risk regions for potential dose escalation with radiotherapy.

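### The primary outcome is the accuracy of individual DCE, DWI and BOLD parameters, but the analysis attaches accuracy measures to a selected model that need not contain any of them

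*Protocol article*

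**What the plan says.** All references are to the protocol article.

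- **Primary outcome section:** "To evaluate sensitivity and specificity of quantitative parameters derived from DCE-MRI, DWI-MRI and BOLD-MRI as predictors of progression-free (local, nodal, systemic) survival at 2 years". The object is the parameters of three named functional techniques.
- **Secondary outcomes:** radiomics has its own entry: "To apply radiomics for derivation of textural imaging features as predictors of progression-free (local, nodal, systemic), overall survival and TVRR".
- **Statistical analysis, single-variable step:** "a univariate logistic regression reporting the OR with 95% CI and p value from the likelihood ratio test will be performed".
- **Statistical analysis, candidates for the multivariable model:** "All covariates (fMRI parameters and radiomic features in table 1) and demographics". Those with p<0.1 enter a forward logistic regression, with p<0.05 then counted as significant.
- **Statistical analysis, accuracy:** "The utility of the final prognostic model will be evaluated using sensitivity, specificity and area under the receiver operating characteristic curve".
- **Sample size and power:** 40 patients, an assumed 2-year recurrence rate of 35% and 14 expected events, with no power calculation.

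**The concern.** The primary outcome asks how well each functional parameter separates patients who progress by 2 years from those who do not. The analysis section answers a different question: how well a model picked by significance testing does so. Nothing keeps a DCE, DWI or BOLD term in that model, and the candidate list lets texture features and demographics compete for the places.

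If the section is followed literally, the main report could give odds ratios for the functional parameters and an accuracy figure for something else. The Future work section plans a validation study and then a randomised study built on the resulting risk model, so it matters whose accuracy the published figures describe.

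**Working it through.** **1. The plan's own figure.** Expected events = 40 × 0.35 = 14, as stated. Non-events = 40 − 14 = 26. This treats every recurrence as a PFS event and assumes complete 2-year status.

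**2. What is reported for what.**

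| Object | OR, CI, p | Sensitivity, specificity, AUC |
|---|---|---|
| Single DCE, DWI or BOLD parameter | stated | not stated |
| Final forward-selected model | – | stated |
| Primary outcome requires | – | sensitivity and specificity of the parameters |

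The accuracy measures sit in the second row; the primary outcome belongs in the first.

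**3. An odds ratio does not fill the gap.** For a parameter cut at a threshold, OR = [Se/(1−Se)] × [Sp/(1−Sp)]. Take 11/14 and 21/26 as an illustration: (11/3) × (21/5) = 15.4. The same OR arises with Se = 50% and Sp = 15.4/16.4 = 94%. One odds ratio fits many pairs of sensitivity and specificity, so reporting it does not report the primary outcome.

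**4. Can the final model lack every functional term?** The text allows it, since no term is forced in. As an illustration only, the stated rule (likelihood ratio p<0.1, then forward selection at p<0.05) was simulated with independent noise predictors, 14 events and 26 non-events, in 300 runs per setting. Candidate counts are assumptions, because the article gives no number of texture features or demographics.

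| Functional / other candidates | No model formed | Model without any DCE, DWI or BOLD term | Mean apparent AUC when a model formed |
|---|---|---|---|
| 6 / 16 | 100 − 71 = 29% | 44% | 0.76 |
| 18 / 18 | 100 − 84 = 16% | 26% | 0.82 |

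The first setting takes the 6 functional parameters of Table 1 (four DCE, one DWI, one BOLD) once each. The second takes them at the three scans, 6 × 3 = 18. With no signal, then, 29 + 44 = 73% or 16 + 26 = 42% of runs end with no accuracy figure that involves a primary-outcome parameter. A real functional signal would lower these shares.

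**5. Precision once accuracy is reported per parameter.** Exact (Clopper-Pearson) limits are the 2.5% point of Beta(x, n−x+1) and the 97.5% point of Beta(x+1, n−x). The counts are illustrative.

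- Sensitivity 11/14 = 79%: 0.492 to 0.953, that is 49-95%.
- Specificity 21/26 = 81%: 0.606 to 0.934, that is 61-93%.

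These widths come from the sample size, not from the mismatch. They are what the corrected analysis would show.

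**The case against.** The best reply is that the section is loose rather than wrong. It lists its analyses separately: functional parameters for PFS are one item, radiomics is another, and the modelling recipe applies to each in turn. On that reading radiomics never enters the primary PFS model. Mention of different thresholds suggests that per-parameter cut-offs are intended, which is where sensitivity and specificity would naturally be computed. The study is exploratory and unpowered, and the patient-level data would still allow the right calculation.

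Part of this stands. Radiomic and demographic terms are candidates, so the model *may* contain them; a reader might infer that it always does, and the text does not support that. The covariate list, whose brackets do not balance, does name functional and radiomic features together, so the separate-models reading is possible but not what the list says. The thresholds appear as regression predictors with no accuracy measure attached. Even with radiomics kept out, accuracy would still belong to a combined model, so the mismatch remains.

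A reader might also infer that the plan wrongly ignores stage, nodal status and histology, since the Introduction cites factors "including histology, grade, hypoxia, vascularity and cellularity that can influence fMRI-derived parameters". The documents do not support that as an error. Demographics is undefined in a condensed article, a full covariate list is commonly left to documents not shown here, and added value over stage is not a stated objective. Forcing in a clinical term is a modelling preference.

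**Conclusion.** The point holds. The article fixes both what the single-parameter step reports and what accuracy is computed on, and neither matches the primary outcome. This is a stated mismatch, not detail left to an unseen analysis plan, and it needs no numerical assumption.

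Its practical size cannot be fixed from the documents. The simulated shares rest on assumed candidate counts, independent predictors and no signal; they show only that a final model without a functional term is not a remote possibility. A reader might infer that the study cannot estimate its primary outcome. That goes too far: the data will be there, and only the written analysis fails to ask for the estimate. The plan should be corrected, but neither the design nor the sample size has to change.

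**What to change.** Amend the Statistical analysis section as follows.

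1. For PFS at 2 years, make the primary analysis the AUC, sensitivity and specificity, each with a 95% CI, of every DCE, DWI and BOLD parameter in Table 1. Fix the time points and cut-offs in advance. If cut-offs are chosen from the data, give optimism-corrected estimates.
2. Label these results exploratory. Six parameters at three scans already give 18 sets of results, before temporal changes, on about 14 events.
3. Keep the multivariable model as a secondary analysis, and say that its accuracy is that of the combination.
4. Fit radiomic features in a separate secondary model, in line with the Secondary outcomes section.

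The cost is more analysis work, including agreement on cut-offs or a correction for choosing them, and intervals as wide as those in the working. No extra patients, scans or samples are needed.

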### Future work

By combining imaging and molecular-based biomarkers, EMPIRIC aims to develop a precise and informative radiogenomic tool, which demonstrates intratumour heterogeneity and in particular regions of radio-resistance within cervical tumours. It will identify relevant parameters and variables from fMRI, biopsy samples and blood samples in the development of predictive and/or prognostic models in cervical cancer radiotherapy. This will allow for further work which will include the development of a larger prospective pilot study aiming to validate this risk stratification model and thereafter a randomised study evaluating the role of personalised dose escalation strategies to fMRI-defined biological targets at the point of brachytherapy delivery based on this risk stratification model.

